### Follow-up and masking

Follow-up data are collected by postal questionnaire. We have implemented an intensive approach to follow-up. Participants are mailed a follow-up questionnaire, and if a response is not received within one week, they are telephoned to ensure they have received the questionnaire. A second questionnaire is mailed if necessary. If there is still no response, the participant is contacted one week later, and a core set of outcomes are collected over the telephone. All follow-up data are collected and analysed by individuals who are independent of the recruitment, randomisation, baseline assessment and are masked from the treatment provision. This level of masking will be maintained until final analysis of the data has been completed. The only exception to this rule will be if the data monitoring committee require unmasked data, and in this circumstance, only the independent Chairperson will be aware of assignments.

### Quality assurance

Trial procedures are audited at regular intervals to ensure compliance with the protocol. Maintaining trial profile and competence in trial procedures is challenging in the ED, because of a high turn-over of staff and a diversity in the staff groups dealing with injuries in different hospitals. To combat these difficulties, training is provided on cycles that coincide with staff rotation, as well as various other time points (e.g. in-service training).

### Data analyses

The analysis will be conducted as intention to treat. An analysis of all people who completed the trial will be undertaken, and in addition, a sensitivity analysis will be undertaken to assess the range of potential biases that could result from loss to follow up or withdrawal. Numerical and graphical summaries of all the data will be compiled, including a detailed description of missing data at the clinic visit, questionnaire and individual level.

Logistic and log-linear multinomial regression models will be used to provide estimates of the recovery rates and the prevalence of residual symptoms, with confidence intervals. As there are multiple centres and repeat assessment, random effect (or hierarchical) models will be used to investigate the components of variation. The common current and cheapest therapy is Tubigrip^®^, so each of the three other treatments will first be compared with it. Any treatments found to be more effective than Tubigrip^® ^will be compared with each other. Regression modelling will allow an assessment of factors that might indicate the appropriate choice of treatment. As these analyses are pre-specified, issues of multiple comparisons are minimal.

The sensitivity of the above analyses to missing data at various levels will be assessed and quantified using modern statistical methods for incomplete multivariate data [19].

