The appropriate technique of economic evaluation will depend on the results of the study [23]. The simplest eventuality would be where the least expensive intervention is found to be better on at least one outcome measure and no worse on any other i.e. dominant. Another is where two interventions have the same outcomes in which case cost-minimisation analysis will be used to compare the two. However, where an intervention is clearly better in terms of outcome but is also more costly, a different approach is required. One accepted method is to compare the different interventions in terms a single outcome measure identified as clinically important for the condition being treated. The primary outcome meets this requirement. Therefore, the costs per unit improvement in mobility will be used to provide an estimate of overall cost-effectiveness; average and incremental (relative to reference treatment) cost-effectiveness ratios will be estimate for the different treatments used. However, this approach does not allow comparison with other types of intervention/condition combinations and also does not consider the value (utility) of differences in improvement in health status. In the present study, the EQ-5D will be used to generate such utility scores that can be compared to costs. A cost-utility analysis will estimate outcomes in terms of differences in quality-adjusted life years (QALYs), representing the period of life subsequent to a health care intervention weighted or adjusted for the quality of life experienced by the patient during that period, and compare these with cost for the four interventions [23]. The cost-utility analysis will present the incremental cost of the extra benefit gained both in summary form in terms of incremental cost per QALY, and also using a 'disaggregated' approach where the extra costs are presented alongside the HRQOL dimensions such as pain.

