### Sample size

Although there was a paucity of published data available to inform the sample size estimate at the outset of the trial, the preliminary phase of the study has enabled us to make a more accurate estimation of the sample size required. The presented estimate is based on a standard sample size calculation for a two-sample t-test with equal variances and a significance level of 0.05, using the variance estimated from an ANOVA of the 4-week data (n = 100). The minimal clinically important difference is set at 10 percent, which represents a small to moderate effect size. A target of 600–650 participants will allow us to detect clinically important outcomes at 4 and 12 weeks. We are powered >90% to detect differences of 10 percent in the primary outcomes, and have sufficient power to detect differences in a range of secondary outcomes at 80% power. To account for the possibility of loss to follow-up, the estimate includes an inflation of 20%. However, the trial should be able to report whether any of the treatments have a sustained negative effect on outcome at 9 months. We are taking a pragmatic approach to estimating the sample size, and the Data Monitoring Committee are reviewing assumptions underlying the calculation at 6-monthly intervals.

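### The stated power of more than 90% is for a difference in mean score, but the only effect models named are for recovery rates, and the 10 percent target has no unit

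*Protocol article*

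**What the plan says.** The Sample size section describes a "standard sample size calculation for a two-sample t-test with equal variances and a significance level of 0.05". Its variance comes from an ANOVA of 4-week data on 100 participants. It continues: "The minimal clinically important difference is set at 10 percent, which represents a small to moderate effect size", and claims: "We are powered >90% to detect differences of 10 percent in the primary outcomes". A t-test with an ANOVA variance describes a mean difference on a continuous score.

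The Economic analysis section also treats mobility as a quantity: "the costs per unit improvement in mobility will be used to provide an estimate of overall cost-effectiveness".

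The Data analyses section takes a different line: "Logistic and log-linear multinomial regression models will be used to provide estimates of the recovery rates", and also of the prevalence of residual symptoms. Random-effect models are mentioned only as a way to study components of variation. No model for a difference in mean score is named. The primary outcome elsewhere in the article is recovery of mobility, so recovery rates most naturally refers to it.

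**The concern.** The power calculation and the named effect models work on different outcome scales. If the analysis is carried out as written, the score has to be turned into categories, and power worked out for a t-test on the score does not carry over.

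The 10 percent adds to the difficulty. Beside a t-test it reads as a difference in score. Beside recovery rates it could be taken for percentage points of recovery, or for a relative change. The article does not say which.

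Power matters at this step because only supports found better than Tubigrip go on to be compared with each other. A useful support missed here drops out of the later comparison. The article also plays down multiplicity on the ground that these analyses are pre-specified, so it relies on this section as its pre-specification.

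**Working it through.** **Inputs from the article.** Total 600–650, significance level 0.05 and a 20% allowance for loss (Sample size); four arms (Economic analysis); each of three supports against Tubigrip (Data analyses).

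**Assumptions.** Equal allocation, two-sided test, normal approximation, and 20% taken off the total: n = 600 × 0.8 / 4 = 120 to 650 × 0.8 / 4 = 130 evaluable per arm. Dividing by 1.2 instead gives 125–135 and leaves the range in the first row of the table in step 2 unchanged.

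**Not given.** SD, control recovery rate, recovery cut-point, unit of the 10 percent.

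**Step 1: the plan's own figure.** Without the SD it cannot be reproduced exactly, so solve backwards:

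d = (1.960 + 1.282) × √(2/n)

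- n = 120: d = 3.242 × 0.1291 = 0.418
- n = 130: d = 3.242 × 0.1240 = 0.402

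Power above 90% needs an SD no larger than 1/0.418 = 2.39 to 1/0.402 = 2.49 times the target difference (23.9–24.9 units if the target is 10 units). That fits an effect called small to moderate, so the claim is plausible for a mean score.

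**Step 2: the same effect with the score cut in two.** For a normal score and control recovery rate p₁ = c, the treated rate is p₂ = Φ(z_c + d). With p̄ the average of the two rates,

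power = Φ{[(p₂ − p₁) − 1.96 √(2p̄(1 − p̄)/n)] / √([p₁(1 − p₁) + p₂(1 − p₂)]/n)}

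Example, n = 120, c = 0.50, d = 0.418: p₂ = 0.662, p̄ = 0.581. The two standard errors are 0.0637 and 0.0628, so power = Φ[(0.162 − 1.96 × 0.0637)/0.0628] = Φ(0.59) = 72%.

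| t-test power | d (n = 120 / 130) | Split score, control rate 20–70% | Control rate 80% |
|---|---|---|---|
| exactly 90% | 0.418 / 0.402 | 64–73% | 55% |
| 95% | 0.465 / 0.447 | 73–82% | 63% |
| 99% | 0.553 / 0.532 | 85–93% | about 76% |

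**Step 3: more than two categories.** A rough approximation for k equal ordered categories multiplies the information of the t-test by (1 − 1/k²) × 3/π. Starting from exactly 90%, it gives 85% for three categories and 87% for four or five. It is generous: for two categories it gives 78%, against at most 73% in step 2. The loss shrinks with more ordered categories but does not vanish.

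**Step 4: the 10 percent read as percentage points of recovery.** The power formula of step 2 with p₂ = p₁ + 0.10:

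- control rate 20–70%: 34–46%
- control rate 10% or 80%: 58–62%

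Example, n = 120, 50% against 60%: Φ[(0.10 − 1.96 × 0.0642)/0.0639] = Φ(−0.41) = 34%. On this reading 90% power would need about 392–524 evaluable per arm at control rates of 30–70%.

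**The case against.** The article condenses a fuller protocol. It assigns no model by name to the FAOS, the FLP sub-scales, the SF-12 or the EQ-5D, so the Data analyses section can be read as an outline. It does not say that scores will not be analysed as scores, and its mention of hierarchical models gives no outcome scale. Costing per unit of mobility suggests that a score analysis may be kept. All of this stands, so it is not certain that the mobility score will be cut. It does not remove the conflict: the section does name effect models, names them for recovery, and they are not what was powered.

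A reader might go further and infer that the trial has only about 35–45% power and would miss an important difference more often than not. The article does not support that. The 10 percent is set beside a t-test, an ANOVA variance and an effect-size description, which point to a mean difference. No recovery-rate difference is given as a target, and the control rate that fixes the figure is absent.

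Nor can 64–73% be taken as the trial's power. The claim is a lower bound, so the t-test power may be well above 90%. The cut-point is unknown, and multinomial models are named as well as logistic ones.

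**Conclusion.** The mismatch holds. The stated power applies to a comparison of mean scores, which the article does not name as an analysis. It does not carry over to the models of recovery rates that the article does name. The unit of the 10 percent also has to be stated.

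The size of the loss is conditional on equal allocation, a two-sided 0.05 test, 120–130 evaluable per arm, a normal score and a single cut. For control recovery rates of 20–70%, power lies between 64% and 93%, depending mainly on how far the t-test power exceeds 90%. In the exactly-90% case the chance of missing the effect rises from 10% to 27–36%. The percentage-point figures in step 4 show why the unit matters; they are not an estimate of this trial's power.

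**What to change.** In Data analyses, name a linear mixed model on the continuous mobility score at 12 weeks as the primary comparison of each support with Tubigrip. Twelve weeks is the assessment that closes the three-month period the article defines as primary. Keep the logistic and multinomial models for outcomes that are categorical by nature, such as residual symptoms and further treatment.

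In Sample size, state the unit of the 10 percent and the SD used, and say that the power of more than 90% applies to the mean-score comparison.

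If recovery rates are meant to be primary, define recovery, give the assumed control rate and restate the power for that analysis.

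This costs wording in two sections and needs no extra patients or data. The article reports recruitment as midway and the Data Monitoring Committee as reviewing the sample-size assumptions every six months, so there is a natural point at which to do it.

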### Baseline and outcome measures

Clinical status is measured at baseline, 4 weeks, 12 weeks and 9 months. The baseline assessment also includes date of birth, sex, body mass index, ethnicity, an assessment of pre-injury abilities including usual levels of mobility, engagement in sporting activity, usual occupation and employment (including hours worked and type of work undertaken) and completion of the baseline version of the outcome questionnaires.

The selection of outcome measures is based on a systematic review completed during the preparatory stage [14], and are shown in Table 1. There is a paucity of information on the psychometric properties of self-completed questionnaires for ankle conditions. The Foot and Ankle Outcome Score (FAOS) is a questionnaire that ascertains functional limitations (including mobility) and the severity of other symptoms after ligament sprains, and has evidence of validity and reliability [10]. Previous versions have been validated against objective tests of ankle function [15]. The Functional Limitations Profile (FLP) is the British version [16] of the Sickness Impact Profile [17]. We are using the FLP occupation and mobility sub-scales to provide more detailed information on the impact of the injuries and treatments including adaptations that occur after the injury. The FLP has not been used in studies of ankle injuries previously. Health related quality of life will be measured using the SF-12 version 1 and EQ-5D [18]. Return to normal occupation and leisure activities will be recorded as the date that people return to work and normal activities. Patients are asked to make a record of significant dates on a calendar to aid recall. The effectiveness of these calendars is being tested in a separate study.

**Table 1 T1:** Outcome measures

**Outcome**	**Outcome measure**
Functional limitations and severity of symptoms after ligament sprains	Foot and Ankle Outcome Score (FAOS)
Impact of injuries and treatments including adaptations that occur after injury	Functional Limitations Profile (FLP) occupation and mobility sub scales
Health related quality of life	Short Form 12 version 1 (SF-12 v1)
Health related quality of life	EuroQol (EQ-5D)
Health economics	Resource Use Questionnaire
Return to normal occupation and leisure activities	Date of return to work and normal activities recorded on a trial calendar

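### Pre-specification does not make multiplicity minimal for the analysis of factors that might guide the choice of support

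*Protocol article*

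**What the plan says.** The Data analyses section of the protocol article sets out a sequence. Each of the three supports is compared with Tubigrip, and any that prove more effective are then compared with each other. Next comes: "Regression modelling will allow an assessment of factors that might indicate the appropriate choice of treatment". The paragraph closes with: "As these analyses are pre-specified, issues of multiple comparisons are minimal".

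The Baseline and outcome measures section lists variables that could serve as such factors, among them "date of birth, sex, body mass index, ethnicity, an assessment of pre-injury abilities including usual levels of mobility, engagement in sporting activity", together with occupation and employment. It does not tie them to the factor analysis.

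The Sample size section rests on a "two-sample t-test with equal variances and a significance level of 0.05" and states: "We are powered >90% to detect differences of 10 percent in the primary outcomes". It says nothing about power for interactions.

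**The concern.** A factor can indicate which support a patient should receive only if it modifies the treatment effect. A factor that is merely prognostic predicts outcome equally under every support and cannot guide the choice. The analysis is therefore a set of treatment-by-factor interaction tests. With four arms, each factor brings three interaction contrasts against Tubigrip.

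The closing sentence offers pre-specification as the reason why multiplicity needs little attention. Pre-specification stops tests from being chosen after the data are seen. It does not lower the chance that one of many tests is positive by accident. That is true whether or not a fuller document names the factors.

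At stake is how a positive interaction may be described. Under this wording, a chance subgroup result could be presented as a pre-specified finding on which support suits whom, with no allowance for the number of factors examined.

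**Working it through.** **Inputs from the article.** Significance level 0.05 (taken as two-sided; sidedness is not stated). Power above 90% for a 10 percent difference. Target 600–650, including a 20% inflation for loss. Four arms.

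**Assumptions.** Equal allocation. Number of factors k from 4 to 8. Factors independent unless stated. Each test at 0.05.

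**1. The article's own power figure.** It cannot be reproduced, because no standard deviation is given. It can be checked for plausibility. With 20% loss, 600–650 randomised leaves 600 × 0.8 / 4 = 120 to 650 × 0.8 / 4 = 130 per arm. The standardised effect detectable with 90% power is (1.960 + 1.282) × √(2/n), which is 0.42 at n = 120 and 0.40 at n = 130. That fits the article's description: "The minimal clinically important difference is set at 10 percent, which represents a small to moderate effect size". The stated power is plausible for a two-group comparison.

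**2. False-positive chance, one joint 3-df test per factor.** With no true effect modification the chance of at least one positive is 1 − 0.95^k:
- k = 4: 1 − 0.815 = 18.5%
- k = 6: 1 − 0.735 = 26.5%
- k = 8: 1 − 0.663 = 33.7%

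**3. False-positive chance, three separate contrasts per factor.** The three contrasts share the Tubigrip arm, so they correlate at 0.5. Simulation with 200,000 draws gives 12.5% for a single factor. For several independent factors:
- k = 4: 41.5%
- k = 6: 55.4%
- k = 8: 65.8%

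As a check, 1 − (1 − 0.125)^4 = 41.4%. If the factors correlate at 0.5 with one another, the three figures fall to about 36%, 45% and 53%.

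**4. Interaction power.** For a binary factor with prevalence q, the variance of the difference between two subgroup treatment effects is the main-contrast variance divided by q(1 − q). For an interaction equal to the minimal important difference:

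Power = Φ[(1.960 + z_P) × √(q(1 − q)) − 1.960],

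where P is the main-effect power. This uses the normal approximation on the scale of the article's t-test.

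| Main-effect power | Factor split | Calculation | Interaction power |
|---|---|---|---|
| 90% | 50:50 | Φ(3.242 × 0.5 − 1.960) | 36.7% |
| 95% | 50:50 | Φ(3.605 × 0.5 − 1.960) | 43.7% |
| 99% | 50:50 | Φ(4.286 × 0.5 − 1.960) | 57.3% |
| 90% | 30:70 | Φ(3.242 × 0.458 − 1.960) | 31.8% |
| 90% | 10:90 | Φ(3.242 × 0.3 − 1.960) | 16.2% |

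At 90% main-effect power and a 50:50 split, an interaction must be twice the minimal important difference to reach 90% power, since 2 × 0.5 = 1 restores the main-effect non-centrality.

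**The case against.** **The article is condensed.** A journal article commonly leaves the factor list, the test and any hierarchy to a fuller document, which is not shown. A reader might infer from the silence that no factors were specified. The article does not support that, and the missing list is no fault here. The stated reason for setting multiplicity aside is still wrong, because naming the factors elsewhere would not control the error rate.

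**The reference is arguable.** The multiplicity sentence might be meant only for the treatment comparisons described just before. That is possible, but the factor sentence stands between, and nothing excludes it. If the narrower meaning was intended, saying so costs nothing.

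**The article sets no decision rule.** The factor sentence is hedged, and no 0.05 threshold or contrast-by-contrast testing is stated for it. This objection stands. A reader might infer that a false effect modifier is more likely than not, or that any guidance would be mostly noise. The first needs about six or more independent factors, or eight correlated ones, each tested through three contrasts; with one joint test per factor the chance stays near a third even at eight. The second was not computed. Nor is the 0.05 in the Sample size section a familywise target for these tests, so multiples of it mean little.

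**The 37% is not a property of the trial.** This also stands. It needs main-effect power of exactly 90%, where the article claims more, plus an even split and an interaction equal to the minimal important difference. A reader might also infer that low power produces the false finding. It does not: it leaves the type I error unchanged and only weakens the credibility of a positive result.

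**Conclusion.** The point holds as a fault in a stated claim. On its natural reading the article extends to the factor analysis a reassurance that pre-specification cannot give. For 4 to 8 independent factors at 0.05, the chance of at least one false effect modifier is about 19–34% or 41–66%, depending on whether each factor gets one joint test or three contrasts. Neither range is minimal. Both depend on an assumed number of factors and an assumed threshold.

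The power result is a second, separate reason for caution. For an interaction equal to the minimal important difference, the cases examined run from about 16% to 57%, with 37% as the benchmark for an even split at 90% main-effect power. Larger interactions would fare better.

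The three main comparisons with Tubigrip are outside this point.

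**What to change.** Limit the multiplicity sentence so that it does not cover the factor analysis, and reword the factor sentence along these lines:

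*Factors that may modify the treatment effect will be examined as exploratory analyses of the primary outcome at the primary time point. For each factor on a short list fixed before unmasking, one joint 3-df treatment-by-factor interaction test will be done. The number of factors tested will be reported, and treatment effects within levels of each factor will be shown with confidence intervals. No recommendation on treatment selection will be made from these results alone.*

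Adjustment across factors, for example by Holm's method, is optional. It would control the familywise rate but reduce already limited power.

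The change is wording only. It needs no extra patients or data, and the article's Conclusions describe the trial as still recruiting. The cost is that an effect-modifier result becomes hypothesis-generating and cannot by itself support practice advice.

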### Treatment allocation

Randomisation is stratified by centre and provided via a phone-in service, which utilises a computer generated random allocation. Allocation concealment, which shields people who enter patients into a trial from knowing future allocations, is thereby ensured. The randomisation service is independently administered and quality controlled by the Birmingham Cancer Trials Unit.

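### Pre-specification does not make multiplicity minimal: three unadjusted comparisons with Tubigrip carry about 2.5 times the nominal error, and the stated power makes no allowance for this

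*Protocol article*

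**What the plan says.** The trial has four arms: below knee cast, Aircast brace, Bledsoe boot, and Tubigrip as reference. Under Data analyses, the article names Tubigrip as the common and cheapest therapy, "so each of the three other treatments will first be compared with it". A second stage follows: "Any treatments found to be more effective than" Tubigrip are then compared with each other. The paragraph closes with "As these analyses are pre-specified, issues of multiple comparisons are minimal". The article mentions no adjustment, testing hierarchy or global test.

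The Sample size section bases the target of 600 to 650 participants on "a standard sample size calculation for a two-sample t-test with equal variances and a significance level of 0.05", with 20% inflation for loss to follow-up. It then states: "We are powered >90% to detect differences of 10 percent in the primary outcomes".

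**The concern.** The closing sentence gives pre-specification as the reason that multiplicity hardly matters. Pre-specification deals with a different problem, the choosing of tests once the data are known. Three planned tests at 0.05 have the same joint error rate whether or not they were written down first.

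This matters because the first-stage results are used. They decide which supports are compared with each other, and the Economic analysis section makes the evaluation technique depend on the trial's results. A false positive could therefore put a costlier support ahead of the cheapest reference. A reader who takes the sentence at face value would also assume that the overall error is close to 5%, and that the stated power holds at that level.

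**Working it through.** **Inputs from the article.** Three comparisons share the Tubigrip control (Data analyses). The significance level is 0.05 with no split, the difference is 10 percent (read here as 10 points), total N is 600–650, loss is 20%, and power is above 90% (Sample size).

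**Assumptions.** The tests are two-sided and allocation is 1:1:1:1; the article states neither. One outcome is tested at one time point. Test statistics are treated as normal.

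**1. The plan's own power.** The SD is not given, so the figure cannot be reproduced. What can be found is the largest SD compatible with 90% for one unadjusted test:

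SD = 10 / [√(2/n) × (1.960 + 1.282)]

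- N = 650: n = 650 × 0.8 / 4 = 130 per arm, SD ≤ 24.9 (standardised difference about 0.40).
- N = 600: n = 600 × 0.8 / 4 = 120 per arm, SD ≤ 23.9 (standardised difference about 0.42).

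The article calls the effect small to moderate, so its power is plausible for a single comparison at 0.05.

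**2. Family-wise error when no support differs from Tubigrip.** With equal arms and a shared control, any two of the three statistics have correlation 0.5. With c = 1.960 and Y standard normal,

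P(at least one |Z| > c) = 1 − E{[Φ((c − √0.5·Y)/√0.5) − Φ((−c − √0.5·Y)/√0.5)]³}

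- Difference in either direction: **12.5%** (simulation also 12.5%). For comparison, three independent tests give 1 − 0.95³ = 14.3%, and the Bonferroni bound is 15%.
- At least one support declared better (upper tail only): **6.3%**, against 2.5% for one test.
- Ratios to nominal: 12.5/5 = 2.5 and 6.3/2.5 = 2.5.

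The second stage applies only to supports found better, so 6.3% is the rate that belongs to that gate. The 12.5% also counts supports falsely found worse than Tubigrip.

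**3. Effect of adjustment on power.** For 5% overall, the Dunnett critical value is 2.349 (0.0188 per comparison). Bonferroni gives 2.394 (0.0167). If unadjusted power were exactly 90%:

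- Dunnett: Φ(1.960 + 1.282 − 2.349) = Φ(0.893) = 81%.
- Bonferroni: Φ(1.960 + 1.282 − 2.394) = Φ(0.848) = 80%.

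The article says more than 90%, however, so the result depends on the SD. Power for 10 points, from Φ(10/[SD·√(2/n)] − critical value):

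| Evaluable per arm | SD | Unadjusted | Dunnett | Bonferroni |
|---|---|---|---|---|
| 130 | 20 | 98.1% | 95.4% | 94.9% |
| 130 | 22 | 95.6% | 90.6% | 89.8% |
| 130 | 24 | 91.9% | 84.4% | 83.3% |
| 120 | 20 | 97.2% | 93.6% | 93.0% |
| 120 | 22 | 94.1% | 87.9% | 87.0% |
| 120 | 24 | 89.8% | 81.0% | 79.8% |

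Dunnett-adjusted power stays at 90% or more if SD ≤ 10 / [√(2/n) × (2.349 + 1.282)]. That is about 22.2 with 130 per arm and 21.3 with 120.

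**The case against.** The strongest reply is that three distinct treatments compared with one reference are three separate questions, and that many statisticians would not adjust across them. The article's aims support this view: they set out to estimate the effectiveness of each support against Tubigrip, and the analysis is to give estimates with confidence intervals. This stands to the extent that adjustment is not compulsory. It does not rescue the sentence, because the article does not make that argument. The reason it gives is invalid, and a fuller analysis plan could add an adjustment without making the printed reason correct.

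Three stronger readings are tempting, but the document does not support them.

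- *The gate has a 12.5% error rate.* It does not. The gate is directional, and its rate is 6.3% under the stated assumptions.
- *The power claim is false and should read about 81%.* That assumes unadjusted power of exactly 90%. With no SD given, power above 90% may survive adjustment, as the table shows.
- *The analyses are not really pre-specified.* A conditional rule stated in advance is pre-specified. When no support differs from Tubigrip, a head-to-head test requires at least two supports to pass, a chance of about 1.1%, and it adds nothing to the family-wise rate. Leaving the factors for the treatment-choice models unnamed is detail commonly left to an analysis plan.

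Nor does the article make a significant result a rule for recommending a support. Cost-effectiveness and cost-utility comparisons also enter that judgement.

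**Conclusion.** The concern holds as a wrong statement in the article, not as missing detail. Pre-specification does not make multiplicity minimal, and an error rate about 2.5 times nominal is not minimal in size either. The 12.5% and 6.3% rest on two-sided 0.05 tests, equal allocation, no true difference between any support and Tubigrip, and one outcome at one time point. The Sample size section refers to primary outcomes in the plural and to both 4 and 12 weeks. Testing more than one of these at 0.05 could raise the rates further, which is not quantified here.

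On power, the supportable conclusion is that the stated figure applies to one comparison and makes no allowance for three. Whether it falls below 90% after adjustment cannot be settled without the SD.

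**What to change.** 1. Delete the sentence on multiple comparisons.
2. Apply a Holm or Dunnett adjustment to the three contrasts with Tubigrip at the primary time point. Alternatively, if error is to be controlled per comparison, say so, give a valid reason, and report the family-wise rate with its assumptions.
3. Report the between-support contrasts with intervals from the same model, and treat claims among supports selected by the gate with caution.
4. State that the power is per comparison, and add the power at the adjusted level using the SD from the 4-week run-in data.

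The cost is a change of wording and a slightly less favourable stated power, with no extra patients. The article describes the trial as mid-recruitment and keeps masking until the final analysis is complete, so the change can still be made credibly before unmasking.
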